## Abstract

**Background:**

Neurodevelopmental difficulties with various emotional and behavioral symptoms increase the risk of mental health problems later in life. Although we know that early detection and interventions are effective, there is a lack of intersectoral, integrative, and evidence-based working models to provide these services for preschool children and their parents. PLUSS (*Psykisk hälsa Lärande Utveckling Samverkan kring Små barn*; English translation: mental health, learning, development, collaboration around preschool children) is a collaborative “one way in” model involving parents, health care providers, preschools, social services, and researchers. PLUSS provides coordinated services to screen, evaluate, and support toddlers with neurodevelopmental problems. It also offers parental interventions and education for preschool teachers.

**Objective:**

The model will be studied in a research project that aims to investigate (1) using a quasi-experimental study on longitudinal trajectories of neurodevelopmental difficulties and ability to function among participating preschoolers, (2) user satisfaction, and (3) implementation of the model and its effectiveness. The long-term goal is to provide evidence-based, coordinated services to reduce problems related to neurodevelopmental difficulties among preschool children and promote well-being and functioning in everyday life.

**Methods:**

The population of interest is children aged 1.5-5 years, whom the child health care nurse refers for further assessment due to suspected neurodevelopmental problems. Data are collected using questionnaires and semistructured interviews. Measures include sociodemographic data, longitudinal data on neurodevelopmental problems, parental well-being and satisfaction, the effectiveness of parental and preschool teacher training and implementation of the model, and fostered multisectoral collaborations. Data will be analyzed with qualitative and quantitative methods.

**Results:**

The PLUSS model has been approved by the National Ethics Review Board (2019–04839). This study was supported by FUTURUM grants 910161 and 910441. Data collection started in April 2019, with the data collection period planned to end in May 2024.

**Conclusions:**

PLUSS is an integrative working model with multiprofessional competence and intersectoral collaboration capacity to help preschool children with neurodevelopmental problems and their parents. It will be studied using quasi-experimental cross-sectional and longitudinal study designs. Data will be collected from parents, health care providers, and preschool teachers, and will be analyzed using quantitative and qualitative methods. The study will run in one Swedish county, and generalizability needs to be studied separately. Loss of follow-up could impact the longitudinal analysis.

**Trial Registration:**

ClinicalTrials.gov NCT04815889; https://clinicaltrials.gov/ct2/show/NCT04815889

**International Registered Report Identifier (IRRID):**

DERR1-10.2196/34969

## Introduction

### Background

Neurodevelopmental problems among preschool children are common, with an estimated 7%-10% prevalence [1]. Early-onset externalizing or internalizing problems predict the later development of mental health problems, corresponding to or overlapping with the initial symptoms [1,2]. The earlier behavioral problems occur in a child’s life, the greater the risk [3,4].

Early identification of children with neurodevelopmental problems is crucial for providing adequate support [1,5]. Despite this knowledge, several Swedish reports have highlighted a dire need for research into the mental health of children of preschool age [6-8]. For example, data on the current prevalence of significant neurodevelopmental problems among Swedish children aged 0-5 years are missing. Inherent to this is how many of these children have been offered and are receiving any kind of intervention. In addition, studies on longitudinal trajectories of problems and provided services are scarce.

In Sweden, child health care is responsible for the early detection and follow-up of developmental problems among preschool children [9]. Swedish child health care has a well-established screening program that reaches 95% of all preschool children [10]. In addition, preschools serve as an environment where children’s problems can be identified, promoting good mental health [11]. Collaboration between child health care and preschools provides a significant opportunity to identify children and families needing support and treatment [12,13]. Standardized assessment methods, such as questionnaires, scales, and observations, with proven reliability are one way to further facilitate the early detection of emotional and behavioral problems related to neurodevelopment [14].

Despite the established health monitoring system, there is no homogeneous system of mental health services for children below school age in Sweden. Regional differences exist, and both public and private service providers are involved. Some children are referred to Child and Adolescent Psychiatry clinics, while others are assessed and followed up on by child habilitation or municipal counseling units [15]. There are also well-known shortcomings in collaborations between health actors and other multisectoral partners such as social welfare services [4]. Coordination of efforts is difficult to establish, and queues of several years for assessment and treatment are frequent.

Efforts to strengthen overall mental health in preschool children appear to have a positive effect later in life [1,16]. A preschool with adequate resources is suitable for health promotion and prevention, with learning opportunities that increase children’s social, cognitive, and adaptive skills [17]. In addition, several studies have shown that group-based parent support programs can improve emotional and behavioral problems among preschool children. However, the long-term efficacy of these programs is uncertain, as are their primary prevention effects [18].

### Theoretical Background of the Study

Theoretically, this project is based on Bronfenbrenner’s socioecological model. According to this model, a child’s development is, apart from genes, influenced by various microsystems (family, preschool teachers, peers, etc), the ecosystem’s support of the family, and preschool structure, as well as by macrosystem-level laws, culture, and policies [19]. Here, concepts such as “person-process-context-time” are highlighted in the proximal process where the person (preschool child) in their approach (play) in his context (preschool/family) develops and learns, for example, interaction over time [20]. Early support to the child, parents, and preschool teachers is expected to promote positive development and increased everyday functioning over time.

A child’s behavior undergoes age-related developmental changes, including progress in motor skills, language, self-esteem, and how to handle emotional regulation. One fundamental skill is self-regulation. It is a multilevel construct that describes the ability of an individual to optimally manage physiological arousal, emotions, attention, behavior, and cognition. Self-regulation helps the child acquire the behavioral, emotional, and cognitive self-control essential for competent functioning and autonomy, both in childhood and life [21]. Acquired developmental skills also support a child’s functioning in everyday life, independent of age. There is an interplay between genes and environmental factors throughout life, including parental support, attachment to caregivers, and the child’s emotional experiences [21]. Furthermore, interactions among preschool children are essential for developing cognitive regulation and coping skills and play a part in equipping children to handle demanding experiences in life [22,23]. Theories of risk and protective factors have determined that it is essential to increase dynamic/impactful health factors as early as possible and reduce the number of risk factors in the child’s context [2].

The overall aim of this study is to study the PLUSS (*Psykisk hälsa Lärande Utveckling Samverkan kring Små barn*; English translation: mental health, learning, development, collaboration around preschool children) model that provides coordinated services to screen, evaluate, and support children (aged 1.5-5 years) with neurodevelopmental problems. The project has the following specific aims:

To study neurodevelopmental issues and the ability to function among preschool children longitudinally.To study parental well-being and satisfaction with provided and used services.To study the implementation of the model and its effectiveness, including parental and preschool teacher training and multisectoral collaborations.

We hypothesize that a coordinated working model with multiprofessional and intersectoral collaborations will promote early detection and support of preschool children with neurodevelopmental problems. We expect that this will also positively impact mental health and well-being in the long run. In addition, we hope that this working model enhances user satisfaction and the effectiveness of processes to provide services.

## Methods

### Setting and Data Collection

The study is based in Jönköping County, in the south of Sweden, and runs within the PLUSS project. The PLUSS model is built upon existing processes for patient flow, from early detection to assessment and interventions. Figure 1 shows the PLUSS flow. Parents of children referred to child health care psychologists due to neurodevelopmental problems are informed about the study by child health care nurses. Parents sign a consent form for participation and fill out questionnaires before the child’s health care psychologist consultation. Subsequently, parents are offered the possibility to participate in a parental training program (PRIMUS). Data are also collected from preschools and preschool teachers who are offered a separate training program. Following the child health care psychologist assessment, and initial parental and preschool teacher training, the child health care psychologist consults the multiprofessional PLUSS to plan and coordinate further evaluations and interventions.

**Figure 1 figure1:**
[figure not shown]
The PLUSS procedure. PLUSS: *Psykisk hälsa Lärande Utveckling Samverkan kring Små barn* (English translation: mental health, learning, development, collaboration around preschool children).

### Study Design and Populations

Inclusion criteria include the following: a child referred to a child health care psychologist, aged 1.5-5 years, with ESSENCE (Early Symptomatic Syndromes Eliciting Neurodevelopmental Clinical Examinations) problems such as developmental delay, interaction, contact difficulties, language and communication difficulties, difficulties in everyday function, concentration/hyperactivity, self-regulation, acting/boundaries, and anxiety [1]. Exclusion criteria include the following: the family only needs parental support and/or there is a risk that participation in PLUSS would delay assessments or referrals to specialized services.

Detailed information about the study is given below. Research within PLUSS focuses on children, parents, and preschool teachers, and professionals working with the PLUSS are included in some substudies. Both cross-sectional and longitudinal quasi-experimental study designs are used. One substudy uses focus group interviews.

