### Sample Size

The aim is to collect data on 700 children. This sample size allows proposed analyses of primary outcomes related to the Strengths and Difficulties (SDQ) instrument as well as subgroup analysis and person-based analysis (cluster analysis and path analysis) with statistical strength of 0.80 and α<.05. Power estimation is based on previous studies by Rothenberger et al [24]. The estimated number of children in the PLUSS pilot project during the first year is 160 children, and for Jönköping County, approximately 860 children per year. Studies on parental training and the user study have estimated sample sizes of n=160 and n=100, respectively. For qualitative studies, a sample size of n=20 is used [25]. Finally, the implementation study will collect data from n=80 professionals and n=100 parents involved in the PLUSS.

The control group (n=160) will be recruited from the parts of the county that have not yet been included in the PLUSS. This means that children/families belonging to the control group receive treatment as usual.

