### Data Analysis

Table 1 summarizes the primary outcomes, confounders, and analysis that will be conducted. Quantitative multivariate analyses will be done in SPSS (version 28; IBM Corp), and longitudinal data will be analyzed using person- and group-centered analytic methods, cluster analysis, and path analysis. A comparison study with the control group and children referred to habilitation centers will occur. The focus group and semistructured interviews will be analyzed qualitatively with content analysis.

**Table 1 table1:** Summary of substudies included in the PLUSS.^a^

Study (design and time frame)	Study population	Informants (instruments)	Main outcomes
User study (qualitative focus group interview study, conducted 2019-2020)	Parents of a 1.5- to 5-year-old child with neurodevelopmental problems (n=13)	Parents (data collected with semistructured focus group interviews)	Satisfaction with health care system
Pilot study on children with neurodevelopmental problems (quasi-experimental quantitative study, conducted 2020-2021)	1.5- to 5-year-old children with neurodevelopmental problems (n=80)	Parents, child health care psychologists, preschool teachers (data collected with SDQ, LAPS, CEQ, JA-OBS, background questions, medical records)	Neurodevelopmental and mental health–related problems: development delay, interaction, contact difficulties, language and communication difficulties, motor difficulties, concentration/hyperactive, self-regulation, acting/boundaries, anxiety Difficulties in everyday function Psychosocial stress factors Socioeconomic status, family constellation, mother tongue, possible diagnosis, education, professional activities The health care process indicators (eg, number of assessments, visits, interventions)
Full-scale study on children with neurodevelopmental problems (quasi-experimental quantitative study with longitudinal follow-up, conducted 2022-2024)	1.5- to 5-year-old children with neurodevelopmental problems (n=160), compared to treatment as usual (n=160)	Parents, child health care psychologists, preschool teachers (data collected with SDQ, LAPS, CEQ, JA-OBS, background questions)	As above

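### An exclusion worded by reference to PLUSS has no stated equivalent for the treatment-as-usual controls, so eligibility may differ between the two groups compared

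*Protocol article*

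**What the plan says.** Study Design and Populations gives one set of criteria, not divided by group. The inclusion criterion is "a child referred to a child health care psychologist, aged 1.5-5 years, with ESSENCE" problems. There are two exclusions. One is for families who need parental support only. The other applies when "there is a risk that participation in PLUSS would delay assessments or referrals to specialized services". The same section describes the designs as quasi-experimental: "Both cross-sectional and longitudinal quasi-experimental study designs are used".

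Sample Size defines the comparator: "The control group (n=160) will be recruited from the parts of the county that have not yet been included in the PLUSS". It adds that "children/families belonging to the control group receive treatment as usual".

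Table 1, under Data Analysis, sets 160 children in PLUSS against 160 under treatment as usual in the full-scale study. Its outcomes are carried over from the pilot and so include health care process indicators such as numbers of assessments, visits and interventions. Instruments adds waiting time for assessment. Data Analysis also mentions a further comparator: "A comparison study with the control group and children referred to habilitation centers will occur".

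**The concern.** The second exclusion depends on what taking part in PLUSS is expected to do to a child's pathway. Where PLUSS is delivered, that question has a natural answer. In a control area no child takes part, so on its plain wording nothing triggers the rule, and the article supplies no substitute.

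Two things are at stake.

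- **Case mix.** A child for whom the PLUSS sequence might delay specialised care is plausibly one with more urgent or complex need. If such children are left out on one side and kept on the other, the groups differ at the start for a reason unrelated to the model's effect.
- **Process outcomes.** The rule removes from the PLUSS group the children in whom delay is foreseen, while waiting time and number of assessments are among the things measured. This is selection on something close to an outcome, and it would matter even if SDQ scores were balanced.

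**Working it through.** **Reading the sections together.** The plan has no figure of its own on this point. Its sample sizes (700 overall, 160 per group) cannot be reproduced, since no effect size or SD is given, but they are not in question here.

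1. The exclusion is defined by PLUSS participation (Study Design and Populations).
2. Controls do not participate in PLUSS (Sample Size).
3. The groups are compared without randomisation (Table 1), so allocation does not balance who is excluded.
4. The article neither waives the criterion for controls nor says that it is to be judged hypothetically for them, or by whom.

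It follows that unequal eligibility is left open. It does not follow that it has occurred.

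**How large could it be?** The article does not report the fraction excluded, its link to SDQ or the stability of SDQ. All three are assumptions below.

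*Baseline shift.* Let severity be standard normal among referred children, with the top fraction q removed from the PLUSS group only. With c the (1 − q) quantile, the mean falls by λ = φ(c)/(1 − q).

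| q | c | φ(c) | λ (SD) |
|---|---|---|---|
| 2% | 2.054 | 0.0484 | 0.049 |
| 5% | 1.645 | 0.1031 | 0.109 |
| 10% | 1.282 | 0.1755 | 0.195 |
| 20% | 0.842 | 0.2800 | 0.350 |

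*Yardstick.* With 160 per group, two-sided 0.05 (sidedness is not stated) and 80% power, the detectable difference is (1.960 + 0.842) × √(2/160) = 0.313 SD. This refers to an outcome comparison, so the baseline shift must first be carried to follow-up.

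*Follow-up level, no true effect, no adjustment.* Let ρ be the correlation of severity with SDQ and r the correlation of baseline with follow-up SDQ. The spurious difference is ρ × r × λ in favour of PLUSS. Its standard error is √((1 + v)/160), with v = 1 − r²ρ²(cλ + λ²). For q = 10% and ρ = r = 1: v = 1 − (0.250 + 0.038) = 0.712, SE = √(1.712/160) = 0.103, ratio 1.89, false-positive rate about 47%.

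Spurious difference in SD (false-positive rate):

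| q | ρ = 1, r = 1 | ρ = 1, r = 0.6 | ρ = 0.5, r = 1 | ρ = 0.5, r = 0.6 |
|---|---|---|---|---|
| 2% | 0.049 (7.4%) | 0.030 (5.8%) | 0.025 (5.6%) | 0.015 (5.2%) |
| 5% | 0.109 (17.5%) | 0.065 (9.1%) | 0.054 (7.8%) | 0.033 (6.0%) |
| 10% | 0.195 (47.0%) | 0.117 (18.9%) | 0.097 (14.4%) | 0.058 (8.2%) |
| 20% | 0.350 (94.0%) | 0.210 (49.7%) | 0.175 (36.2%) | 0.105 (15.8%) |

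*Unadjusted change from baseline.* The PLUSS group starts lower by ρλ and ends lower by rρλ, so its change looks worse by (1 − r)ρλ. For q = 10%, r = 0.6 and ρ = 1 this is 0.4 × 0.195 = 0.078 SD against PLUSS.

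*Same criterion in both areas.* The shift due to this criterion is 0 SD.

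**The case against.** The strongest reply is that the criteria form a single shared list, conditionally worded, so a professional in a control area could ask whether PLUSS would delay this child's care if it were available. How criteria are operated in each area is also detail that an article may leave to the full protocol. The hypothetical reading is possible and prevents any statement that the rule can act only in the PLUSS group. But nothing in the article requires that reading. The difficulty lies in how the criterion is worded, so it is more than an omitted detail.

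A reader might infer that the most severe children are removed from PLUSS and that any difference found could be entirely due to this. The article does not support that. It sets no severity threshold and reports no number excluded. SDQ measures behavioural problems, and a child needing prompt specialist work-up may score moderately. The other exclusion, for parental support only, may remove milder cases and can be applied in both areas.

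The plan also has some protection. Parents complete questionnaires before the psychologist consultation, and Data Analysis refers to confounders and to multivariate and longitudinal methods. Baseline SDQ imbalance is therefore visible and partly correctable. What adjustment cannot be relied on to correct is urgency that predicts the later course beyond baseline SDQ, or the selection bearing on process outcomes.

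A reader might also infer that the habilitation comparison has the same flaw. The single sentence on it does not say how those children are selected, or whether an effect estimate is intended, so the point is not extended to it.

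**Conclusion.** The point holds as a risk that the wording creates, and not as a demonstrated bias. Applied as worded, the exclusion gives the two groups of the only treatment-as-usual comparison different entry rules, probably related to urgency or severity, and it selects the PLUSS group on expected delay.

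Its size is unknown. Under one-sided, exact removal of the top 5%, 10% or 20%, the baseline shift is 0.11, 0.20 or 0.35 SD. Only the last exceeds the 0.313 SD that 160 v 160 can detect, and only if severity is SDQ itself and is fully stable. Under weaker assumptions (10% removed, ρ = 0.5, r = 0.6) the follow-up difference is 0.06 SD, with a false-positive rate of about 8%. At 2% removed the rate stays between 5.2% and 7.4%.

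The direction is not fixed either: unadjusted follow-up levels would favour PLUSS, and unadjusted change scores would count against it. For the process outcomes no size can be given from the document. Without a record of who was excluded in each area, the size could not be judged afterwards.

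**What to change.** Leave the care decision untouched and change only what defines the analysis set.

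- Word the analysis-set criterion without reference to PLUSS, for example whether the child would be sent directly to specialised services at referral.
- Apply and log it in the same way in PLUSS and control areas. Results dates the start of full-scale data collection to May 2021, so for children already enrolled use referral records where possible.
- Report the number excluded, by reason and by area.
- Adjust the 160 v 160 comparison for the baseline SDQ already collected.

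The cost is a short form or record check in control areas, and a few control children leave the analysis set. Retrospective classification from records will be less complete than a form at referral and should be reported as such. Other differences between the areas remain, as in any non-randomised comparison.

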### Sample Size

The aim is to collect data on 700 children. This sample size allows proposed analyses of primary outcomes related to the Strengths and Difficulties (SDQ) instrument as well as subgroup analysis and person-based analysis (cluster analysis and path analysis) with statistical strength of 0.80 and α<.05. Power estimation is based on previous studies by Rothenberger et al [24]. The estimated number of children in the PLUSS pilot project during the first year is 160 children, and for Jönköping County, approximately 860 children per year. Studies on parental training and the user study have estimated sample sizes of n=160 and n=100, respectively. For qualitative studies, a sample size of n=20 is used [25]. Finally, the implementation study will collect data from n=80 professionals and n=100 parents involved in the PLUSS.

The control group (n=160) will be recruited from the parts of the county that have not yet been included in the PLUSS. This means that children/families belonging to the control group receive treatment as usual.

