## Discussion

### Principal Findings

Expected results from this study include estimates of the prevalence of neurodevelopmental problems in preschoolers, their impact on functional ability, and parental well-being. In addition, the effectiveness of the PLUSS working model is elucidated. Qualitative studies are expected to give us information about parents’ and preschool teachers’ experiences related to children with neurodevelopmental problems and how the system can support these children.

A research project conducted within ongoing clinical work provides an excellent opportunity to improve health care but is also affected by everyday obstacles. Not all activities and departments are accustomed to participating in clinical research work, and additional assignments for staff might cause skepticism to arise. The longitudinal study design will allow an analysis of changes over time in the same study participant, providing more substantial evidence for causality than could be obtained from a cross-sectional design. However, loss to follow-up may occur. Combining quantitative and qualitative approaches provides an excellent opportunity to understand the actual change in a child’s behavior with satisfaction and well-being. Another strength is that collaboration and organizational measures are studied in PLUSS.

The project is based at Jönköping County’s health care, collaborating with preschools and social services and researchers from Linköping University. Children and parents are not directly involved in the study design, recruitment, or conduct of the research. Parents are, however, engaged in focus groups that give, for example, input on how the parent educating group should be designed and what it should contain. The focus groups will involve parents of children with neurodevelopmental problems and obtain support from child health care and specialist health care. This study will be made available to the participants, the funders, professionals, researchers, and policy makers.

An important aim for future research in the PLUSS model is to follow the included children long term regarding symptom development, set diagnoses, and evaluate given interventions. Parental stress and perceived competence of parents of children with neurodevelopmental difficulties will also be considered in future research.

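### The 0.80 power is claimed for 700 children, a size no listed substudy has, and it cannot be carried over to the planned 160 versus 160 comparison

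*Protocol article*

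**What the plan says.** The only power statement is in the protocol article, Methods, Sample Size. It begins "The aim is to collect data on 700 children. This sample size allows proposed analyses of primary outcomes" and names the SDQ as the instrument. It then extends the same figure to subgroup analysis and "person-based analysis (cluster analysis and path analysis) with statistical strength of 0.80 and α<.05". No effect size or SD is printed; the basis is a cited earlier study. The same section sets the control group at 160, drawn from parts of the county not yet in PLUSS.

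Table 1 (Methods, Data Analysis) gives the full-scale quasi-experimental study as "1.5- to 5-year-old children with neurodevelopmental problems (n=160), compared to treatment as usual (n=160" and the pilot study as "1.5- to 5-year-old children with neurodevelopmental problems (n=80". No power is stated for either. On the pilot, the Sample Size section says "The estimated number of children in the PLUSS pilot project during the first year is 160 children".

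On attrition, the Discussion (Principal Findings) says only "However, loss to follow-up may occur".

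**The concern.** A power figure belongs to a particular analysis with particular group sizes. Here it is attached to a total that matches no study in the article's own table, and the one controlled comparison with stated sizes has fewer than half as many children. Effectiveness of the model is one of the stated aims, so a reader will naturally look to the 0.80 when judging a PLUSS versus treatment-as-usual result. A null result could then be credited with a sensitivity that was stated for a different sample.

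The same 0.80 is also spread over four kinds of analysis. At any one effect size, a subgroup analysis has less power than the whole-sample analysis. Cluster analysis as such tests no hypothesis, so a power of 0.80 for it has no clear meaning.

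**Working it through.** **Can the 700 be reproduced?** No. The article prints no effect size, SD, sidedness, allocation or loss rate for it. The check is therefore whether 700 matches the listed studies, and what the listed sizes can detect.

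**Step 1. Children in Table 1.** Pilot 80; full-scale 160 + 160 = 320. Sum: 80 + 320 = 400. The controlled comparison is 320/700 = 46% of the stated target.

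**Step 2. Detectable difference.** Assumptions: two-sided α=.05 (the article does not state sidedness), 80% power, independent children, equal SDs, no baseline adjustment, normal approximation. In SD units:

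d = (1.960 + 0.842) × √(1/n1 + 1/n2)

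| Split | √(1/n1 + 1/n2) | d |
|---|---|---|
| 540/160 (700 in all, controls at 160) | 0.0900 | 0.25 |
| 160/160 (Table 1) | 0.1118 | 0.31 |
| 128/128 (160 per group less 20%) | 0.1250 | 0.35 |

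The 20% loss is illustrative; the article gives no rate. With 10% or 30% loss, d is 0.33 or 0.37. An equal split of 700 (350/350) would give 0.21, but the fixed control group of 160 rules it out.

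**Step 3. Does the 0.80 carry over?** Suppose 700 as 540/160 gives exactly 80% power, which means d = 0.252. For 160/160:

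power = Φ(0.252/0.1118 − 1.960) = Φ(0.296) ≈ 0.62

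One-sided, the corresponding figure is 0.64.

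**Step 4. Subgroups.** An interaction across two equal halves has twice the standard error of the main effect. At 160/160 the detectable interaction is 2 × 0.313 = 0.63 SD.

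**Step 5. Sensitivity to what the 700 was sized for.** If it was sized for a half-sample subgroup (270/80), then d = 2.802 × √(1/270 + 1/80) = 2.802 × 0.1273 = 0.357. For that effect the whole 160/160 comparison has power Φ(0.357/0.1118 − 1.960) = Φ(1.23) ≈ 0.89. The 62% is thus conditional on Step 3's assumption.

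**The case against.** The strongest reply is that the Sample Size section never assigns the 0.80 to PLUSS versus treatment as usual. The first aim is longitudinal description and the Discussion expects prevalence estimates, so 700 could be a wider cohort pooled over several years. With about 860 children a year in the county, that is feasible. This stands as a possible reading, but the article describes no such cohort, and on that reading the controlled comparison has no stated power at all.

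A second reply is that a condensed article may leave the effect size and attrition allowance to the full protocol. That also stands. Their absence is not the point; the mismatch between two printed sample sizes is.

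Third, 0.31 SD is pessimistic for a longitudinal study. Under an assumed baseline correlation of 0.5, adjustment lowers it to 0.313 × √(1 − 0.25) = 0.27.

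Some stronger readings are tempting but unsupported:

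- **That no make-up of the sample can reach 700.** Adding 160 separate PRIMUS families and taking the pilot as 160 gives 160 × 4 = 640. That is not a ceiling, because the habilitation comparison group has no stated n and the families' overlap with other substudies is not described.
- **That one sample size cannot give 0.80 to both main and subgroup analyses.** It can, at different effect sizes or if sized for the harder one.
- **That the power claim for path analysis is meaningless.** Path coefficients are tested and can be powered.
- **That the two pilot figures contradict each other.** The 160 stands beside the county's yearly volume and may be patient flow, with 80 the substudy sample.

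**Conclusion.** The point holds as an internal inconsistency. The 0.80 is attached to 700 children; Table 1 describes no study of that size and plans the controlled comparison as 160 versus 160. The stated power cannot be carried over to that comparison. In size, 160 versus 160 detects about 0.31 SD, against 0.25 SD for 700 with 160 controls. If 700 was sized to give exactly 80% for the main contrast, 160 versus 160 has about 62% for the same effect.

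A reader might infer that the comparison is underpowered. The article does not support that: it gives no effect size, and 160 versus 160 reaches 80% if the true difference is about 0.31 SD or more and nobody is lost. The figures rest on two-sided α=.05, independent children, equal SDs and no baseline adjustment; the 0.35 SD rests further on an illustrative 20% loss.

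**What to change.** In the Sample Size section:

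1. Say which children make up the 700 and which analyses the 0.80 refers to.
2. State the detectable SDQ difference for 160 PLUSS versus 160 treatment as usual: about 0.31 SD at 80% power and two-sided α=.05 before loss, then restated with the sponsor's own expected loss.
3. Remove cluster analysis from the power claim.
4. Label subgroup analyses exploratory, unless their own detectable effect is given.
5. Explain how the 160 children in the pilot project relate to the pilot study's 80.

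The cost is that the stated power becomes less favourable. The restatement needs no extra participants. Whether about 0.31 SD is a difference worth detecting is for the sponsor to judge once it is on the page.
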